## 6.3 STUDY INTERVENTION COMPLIANCE

The study team will measure and monitor compliance by reviewing the reports submitted by caregivers and teachers and the reports reviewed by providers. The study team will summarize the RAMP utilization as follows:

- Cumulative number of RAMP Reports completed by caregivers
- Cumulative number of RAMP Reports were completed by teachers

- Cumulative number of RAMP Reports were reviewed by providers

The submission of reports will be time-stamped in the REDCap database system. Additionally, caregivers will be asked to provide the diagnostic assessments at study enrollment, and caregivers will be asked to submit a [study assessment](#) at the study end-point (at 90 days).

## 7 STUDY INTERVENTION DISCONTINUATION AND PARTICIPANT DISCONTINUATION/WITHDRAWAL

### 7.1 DISCONTINUATION OF STUDY INTERVENTION

A participant may be discontinued from study intervention by the site PI. For this study, participants will be discontinued if any of the following occur. Participants may be withdrawn from study due to an AE/SAE, or if remaining in the study is no longer in their best interest. Given the age of participants in this study, pregnancy is unlikely. However, in the unlikely event pregnancy were to occur, the child would be withdrawn from the study. While the RAMP intervention would not affect a pregnancy in any way, a patient would likely be referred to a psychiatrist or obstetrician for stimulant cessation or management.

### 7.2 PARTICIPANT DISCONTINUATION/WITHDRAWAL FROM THE STUDY

Participants (caregiver/child dyads) may choose to withdraw from the study at any time. Their end date and reason for withdrawal if shared will be noted in OpenClinica. Those who exit the study will return to usual, provider-directed care. Their access to the platform will be discontinued.

The study team will consider the following to be an early-terminated participant: any caregiver who completes the informed consent process and enrolls in the study but later withdraws their consent, or the site investigator removes the participant from the study. Participants may withdraw from the study at their own request (e.g., participant chooses to decline any further ADHD treatment), or the site investigator, Data Safety Monitoring Board (DSMB), or DCOC can withdraw a participant. If a participant withdraws from the study, site coordinators or investigators can ask the participant why they chose to withdraw. Research coordinators will document the reason for withdrawal.

The text messages sent from the RAMP will give recipients the option to reply “STOP” to opt-out of the text messaging service. If a caregiver or provider participant opts-out of the text messaging service in this way, a study coordinator will reach out to them to confirm they no longer want to receive text messages from the platform. Participants that confirm they wish to opt-out of receiving text messages will be withdrawn from the study. Withdrawing a participant from the study will not remove the information already collected about that participant from the study. Teachers will not be contacted if they opt-out of receiving text messages from the RAMP, and this will not affect the caregiver/child dyad’s participation in the study.

If a provider participant leaves the practice or withdraws consent to participate, a phone call with the principal investigator, provider, and research coordinator will be held. All children enrolled in the study who are cared for by the provider will be reviewed to determine strategies for continuation in the study.

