Providers will receive ADHD Best Practices education at the start of the study including recommended use of the Vanderbilt Assessment and appropriate follow-up as well as how to utilize the RAMP platform. The project is not focused on the effect of provider training, as these are not new guidelines, but rather addresses other potential barriers that are unique to rural settings. After enrollment of caregiver/child participant dyads, providers will be alerted by their preferred means (text or email) when new RAMP Reports are available for review. Following RAMP report review, the provider will answer a brief 2-question, survey regarding their response to the report. Providers will be able to view the individual as well as prior reports in their dashboard view.

Research coordinators will monitor caregiver and teacher activity, including providing RAMP Report responses and provider activity in reviewing responses, and following up with caregivers and providers as outlined in the retention plan to determine if there have been gaps in or a lack of engagement.

The control group caregiver participants will receive digital education handouts about age-appropriate general pediatric health topics (e.g., exercise, digital media, sleep) weekly for 4 weeks then monthly for 2 months (the same interval as RAMP requests in the intervention group).

- |                                                                                                                                                                                                                                                                      |
|----------------------------------------------------------------------------------------------------------------------------------------------------------------------------------------------------------------------------------------------------------------------|
| 

• Clinical assessment: any paper assessment or RAMP Report reviewed by health care provider

• Study assessment: Vanderbilt Assessment at Day 90, reviewed only by study team

 |
|----------------------------------------------------------------------------------------------------------------------------------------------------------------------------------------------------------------------------------------------------------------------|

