| Evaluate completion of clinical assessments by caregivers and teachers. | Number of completed caregiver and teacher clinical assessments (RAMP Report or paper assessment) that are returned to provider | The level of ongoing caregiver and teacher engagement in each arm will be important for planning a full-scale trial. Absolute number will be used as this is what has been shown to improve ADHD symptom control.  Increasing communication between caregivers and providers is important in enhancing the care of individuals with ADHD and literature in this area in rural settings is lacking. |
| Secondary                                                                             |                                                                                                                                       |                                                                                                                                                                                                                                                                                                                                                                                                                 |
| Evaluate provider acceptability of the RAMP through utilization measures.      | Proportion of provider review surveys with at least one available RAMP Report where review is documented                              | Because improvement in care requires bi-directional communication, the review of newly available reports by the provider will be important to measure. While we anticipate that providers will find accessing this information easy and helpful, it may be difficult to incorporate into usual workflow.                                                                                                        |

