**RAMP Reports completed by caregivers:** The RAMP caregiver interface includes monitoring of ADHD symptoms, engagement in behavioral health care visits, and progress in educational settings. These domains of information have been selected as they are typically combined by providers when making decisions regarding medication dose adjustment. The requests for reports will be sent to caregivers as a link in a text message. Upon clicking the link, they will be able to select radio button responses to questions directly on their mobile device (without any login requirement). The RAMP Report requests will be sent weekly for 4 weeks then every month for the remaining 2 months. RAMP Reports will be submittable for 72 hours after initial release. Once a new RAMP Report is available, caregivers cannot go back and complete reports for prior periods.

**RAMP Reports completed by teachers:** Caregivers in the intervention group will provide teachers with a secure, unique link to access the RAMP Platform. This link will be in the form of a QR code which can be printed on paper or emailed directly to the teacher from the caregiver. Teachers will enter the symptom information directly into the platform. The teacher's RAMP Reports are identical to caregiver RAMP Reports, will consist of the first 18 inattention/hyperactivity questions on the Vanderbilt Assessment, and will be requested at the same interval as the caregivers. We will use an approach similar to that used by Power *et al.* The responses to the teacher RAMP Reports will be available to the providers on the RAMP portal. If a child's teacher does not want to use the RAMP platform, the child will not be disqualified. If a child has multiple teachers, the caregiver should choose one teacher to participate, preferably the one that spends the most time with the child.

[figure not shown]

**Provider Report Review:** Providers will be alerted by their preferred means (text or email) when new caregiver or teacher reports are available for review. While providers will have access to the platform at all times, there will be one provider survey to document review for any given week that there is either a caregiver survey, teacher survey or both to review. .

| Record ID | DDP New Items from RDW    | Basic Demography Form | initial Vanderbilt | clinician review | 1 week RAMP | clinician review | 2 week RAMP | clinician review | 3 week RAMP | clinician review |

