### 9.4.3 ANALYSIS OF THE SECONDARY ENDPOINT(S)

The secondary endpoint, proportion of provider review surveys with at least one available RAMP Report where review is documented, is only relevant to the subset of participants randomized to the RAMP intervention group. There is no formal hypothesis testing for this secondary objective. The proportion of provider review surveys with at least one available RAMP Report where review is documented will be estimated along with the corresponding 95% confidence interval using the Wilson score interval or other method appropriate to the data characteristics.

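### Section 7.2 withdraws a provider who opts out of RAMP texts, although sections 1.1 and 6.1.1 allow providers to be alerted by email instead

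*Protocol*

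**What the plan says.** Section 7.2 of the protocol gives recipients of RAMP texts the option to reply STOP. It then says: "If a caregiver or provider participant opts-out of the text messaging service in this way, a study coordinator will reach out to them" to confirm the wish. The consequence follows: "Participants that confirm they wish to opt-out of receiving text messages will be withdrawn from the study". Providers are named in the first sentence, and the second makes no exception for them. No change of alert channel is offered.

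The description of provider review in section 6.1.1 says: "Providers will be alerted by their preferred means (text or email) when new caregiver or teacher reports are available for review". The synopsis, section 1.1, agrees: after dyads are enrolled, "providers will be alerted by their preferred means (text or email) when new RAMP Reports are available for review". Section 6.1.1 adds that providers can reach the platform at any time.

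The last paragraph of 7.2 deals with a provider who departs from the practice or withdraws consent. It calls for a telephone call and a review of each enrolled child under that provider, to settle how the child continues. Withdrawal through a text opt-out is not listed as a trigger.

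The secondary objective in section 3 is: "Evaluate provider acceptability of the RAMP through utilization measures". Section 9.4.3 measures it as the "proportion of provider review surveys with at least one available RAMP Report where review is documented", in the intervention arm only, without a hypothesis test and with the "corresponding 95% confidence interval using the Wilson score interval or other method appropriate to the data characteristics".

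**The concern.** For caregivers, the text message is how report requests arrive, so there is some logic in ending participation when texts are refused. For providers, a text is only one of two ways of announcing that a report is waiting. The same sentence is applied to both groups, and it fits the second badly.

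Three things are at stake. First, a provider who is willing to go on reviewing reports can be lost over a preference about notifications. Second, that provider's enrolled children are left without the review that 7.2 arranges for other provider departures. Section 5.1 requires the child to be under a participating provider, and section 2.3.1 lists reports not reviewed in time as a risk to participants. Third, refusing the alerts is a plausible sign of low engagement, and section 3 itself anticipates that review may be hard to fit into a provider's workflow. A rule that withdraws those providers acts on the group whose acceptance the secondary objective is meant to describe.

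**Working it through.** This point turns mainly on setting the passages side by side.

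1. *Who is affected.* A provider who chose email receives no RAMP text and has nothing to answer with STOP. The rule therefore reaches only a provider who chose text, later replies STOP, and confirms this to the coordinator.
2. *What then happens.* Under 7.2 the provider is withdrawn. Under 1.1 and 6.1.1 the same provider could have had email alerts from the start and remained in the study. Two providers with the same final preference are treated differently because of their first choice of channel.
3. *What happens to the children.* The two triggers for the review in 7.2 are departure and withdrawal of consent. A confirmed text opt-out is neither on its face.
4. *What happens to the endpoint.* Section 6.1.1 provides one provider survey for each week in which a caregiver or teacher report, or both, is available. Section 9.4.3 takes surveys with an available report as the base. Section 9.3 applies the analysis populations, including all randomized participants, to provider acceptability. Nothing in these sections removes a survey because the provider has been withdrawn.

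The protocol gives no figure for provider opt-outs and no precision for the secondary endpoint, so there is no stated figure to reproduce. The endpoint's base can be bounded. With 18 dyads per arm (section 9.2) and 4 weekly plus 2 monthly requests (section 6.1.1), there are at most 18 × 6 = 108 survey occasions. If 52.7% of occasions yield a report (section 9.2 expects about this return rate; applying it per occasion is my assumption), about 108 × 0.527 = 57 remain.

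The following shows why no single effect size can be given. Suppose that a withdrawn provider reviews nothing, has *k* of the 18 RAMP children, that surveys are equal per child, and that the other providers review a proportion *q*. Keeping that provider's surveys as not reviewed gives *q*(18 − *k*)/18. Dropping them gives *q*. The gap is *q* × *k*/18.

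| *k* | gap if *q* = 0.80 | gap if *q* = 0.60 |
|---|---|---|
| 1 | 4.4 points | 3.3 points |
| 2 | 8.9 points | 6.7 points |
| 4 | 17.8 points | 13.3 points |
| 6 | 26.7 points | 20.0 points |

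If one unreviewed occasion in six precedes the withdrawal and only later surveys are dropped, the dropped figure becomes *q*(18 − *k*)/(18 − *k* + *k*/6). At *q* = 0.80 the gaps are then 3.7, 7.3, 14.1 and 20.5 points. Every value of *q* and *k* here is assumed, and the gap arises only if surveys are dropped, which the protocol does not direct.

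**The case against.** The strongest reply is that the rule is narrow and the endpoint is sound as written. Only a text user who replies STOP and confirms is affected, and the documents give no sign that this will be common. The base in 9.4.3 depends on whether a report is available, not on the provider's status. Section 4.3 already foresees surveys that a provider fails to complete. The plain reading is that a later week with a report and no documented review counts as not reviewed. Sections 9 and 9.4.1 leave detailed analysis to a separate SAP, which is not at hand, so silence on scoring is no fault of the protocol. Section 9.4.8 already tabulates participants who discontinue, and section 1.1 counts providers as participants for the secondary objective. The endpoint is descriptive, in a pilot of 36 dyads.

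Most of this stands, and it rules out a stronger reading. A reader might infer that withdrawn providers leave the denominator and that the review proportion is overstated by 6 to 12 points for each of them. The arithmetic behind such a range is correct: with others reviewing 70% and one of 12, 9 or 6 equally loaded providers withdrawn, the gaps are 0.70/12 = 5.8, 0.70/9 = 7.8 and 0.70/6 = 11.7 points. But the 70%, the equal caseloads and withdrawal before any review are all assumptions, and the exclusion is prescribed nowhere. If the provider had reviewed at the common rate until halfway, the range would halve to about 3 to 6 points.

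The reply does not remove the withdrawal rule. That is a stated rule in the protocol, not a matter an SAP would ordinarily change, and it does not fit the choice of channel in 1.1 and 6.1.1.

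**Conclusion.** The point holds as a conflict over provider withdrawal. Section 7.2 withdraws a provider for refusing one of two permitted alert channels, and it does not name that case among the triggers for reviewing the provider's children. This can selectively remove less engaged providers from a study whose secondary objective is provider acceptability.

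The size cannot be derived from the document. It depends on how many providers choose text, how many then opt out, how many RAMP children each of them has, and how the later surveys are scored. Even the direction depends on scoring. If surveys after withdrawal were dropped, losing low reviewers would raise the proportion. If they are kept, as the plain reading of 9.4.3 suggests, withdrawing a willing provider would record non-review that the rule itself caused. It would go too far to conclude that the endpoint is biased upward as written, or that a provider who simply prefers email is lost: one who chose email at the start is untouched.

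**What to change.** In section 7.2, limit withdrawal on a confirmed text opt-out to caregivers. State that a provider who opts out of texts is moved to email alerts and stays in the study, and that a provider is withdrawn only on withdrawal of consent or departure from the practice. The existing review of the provider's children then covers every remaining route by which a provider leaves. Report the numbers of provider text opt-outs and provider withdrawals beside the review proportion.

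As an optional clarification, which the SAP may already contain, confirm that a week with an available RAMP Report stays in the denominator, and counts as not reviewed if no participating provider documents review.

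The cost is a few sentences. Email alerts to providers are already planned, so the text calls for no new alert channel. The downside is that the reported proportion may be lower, since less engaged providers remain in the study and their unreviewed weeks count.

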The entire timeline will span 17 months with three phases. In the first phase of the study, the providers from the participating practices will receive ADHD Best Practices education and training in the portal use, and will be asked to provide informed consent. A member of the clinic staff (nurse, medical assistant or practice manager) will be identified as site champion. The site champion will facilitate communication between the site study team and the clinic staff. The second phase of the study will focus on child/caregiver and provider utilization. Providers will identify patients with a diagnosis of ADHD who are being started on stimulant medication to be contacted by study staff for enrollment. Research coordinators will discuss the study, perform eligibility screening and obtain consent (if deemed eligible by PI). The consented caregiver/child dyads will be randomized to intervention (requests to submit the RAMP Reports for 3 months) or control (usual care with attention control) groups. Families will be approached until 36 caregiver/child dyads are enrolled (only one child in a family may be enrolled). Each practice will have 6 weeks to enroll 9 participants. After the 6 weeks, practices with low enrollment will receive additional supports. Each week, progress to target will be evaluated to determine if any practice needs additional resources. If multiple practices do not meet enrollment goals, the study team may consider relaxing exclusion/widening inclusion criteria (ex. include patients undergoing re-titration, widen age criteria) and/or opening enrollment. Enrollment will be paused for 3 months from the last month of school to the start of the new school year (beginning of May to end of July). This will decrease the burden on practices and study staff during the time of the year with the fewest number of ADHD diagnoses. Once enrolled, caregiver/child participants will be randomized to either the intervention or control group and followed for approximately 3 months. Participants randomized to the intervention group will submit RAMP reports weekly for 4 weeks and then monthly for 2 months. Participants randomized to the control group will receive digital education handouts at the same frequency as the RAMP reports in the intervention arm. Research coordinators will periodically review the child participant's EMR and mark how many paper symptom assessments are returned while enrolled on the study for both groups. Research coordinators will also access the RAMP platform to log RAMP reports returned by caregivers/teachers, RAMP reports reviewed by providers, and provider survey results. All caregiver participants will complete a 90-day Vanderbilt Assessment as a retention measure (see section 1.2.1 for more details). This phase will continue until all 36 participants have completed their 3-month study period. In the third phase, the above endpoints will be calculated, the full-scale trial will be designed, and the findings presented in a manuscript.

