**Rationale for randomizing at the patient level:** RAMP is an automated communication tool designed to eliminate the work burden for providers of requesting and receiving ADHD symptom data from participants. Thus, providers will not be able to reproduce the RAMP intervention for control participants. However, this is an unblinded pilot, and we do not expect providers to change their patient counseling based on participant condition allocation. Therefore, providers should not be confused by receiving RAMP Reports for some study participants (in the experimental condition) and not receiving RAMP Reports for others (in the control). While providers may increase the frequency of their self-initiated outreach to control participants because of the frequency with which they receive RAMP Reports for experimental condition participants, this bias would likely result in more Type II (false-negative) errors for determining intervention effectiveness, which is preferable to Type I (false-positive) errors.

**Rationale for using digital education handouts:** The digital education handouts will be sent via email to the control group and will serve as an attention control. They will consist of information regarding a general pediatric health topic and will be emailed at intervals matching the RAMP requests in the intervention group.

**Rationale for the schedule of [study assessments](#):** The study team will collect the diagnostic assessment from both the intervention and control groups at 0 months (enrollment), as well as a [study assessment](#) (not shared

with provider and clearly marked as such) at Day 90 (-30/+15) — the study final participant follow-up. The diagnostic assessments will be on paper and will be obtained from the diagnosing provider with caregiver permission. The subsequent [study assessments](#) will be obtained either on paper or electronically (caregiver choice). These [study assessments](#) will serve as markers of retention. Caregiver participant incentives will be based on return of these [study assessments](#).

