## 6 STUDY INTERVENTION

### 6.1 STUDY INTERVENTION(S) ADMINISTRATION

#### 6.1.1 STUDY INTERVENTION DESCRIPTION

**Research Coordinator Procedures:** A research coordinator will be identified at each of the participating ISPCTN sites to organize study procedures at the practices in their state. In the first phase, they will work with site champions at the practices to assist with scheduling the ADHD Best Practice education, RAMP platform orientations, and informed consent encounters for all providers who care for children with ADHD. In the second phase, they will describe the study to interested caregivers and complete enrollment and randomization procedures as well as complete periodic chart reviews and participate in study-related calls. Prior to the start of the first phase, they will receive training in obtaining informed consent if not experienced, given scripted language to use with families when describing the study and supporting caregivers and providers who have not completed or reviewed reports, respectively.

**Provider Training:** All providers who care for children with ADHD within the study practices will be offered ADHD Best Practice education and RAMP orientation as an introduction to the study. Providers will provide informed consent prior to the start of caregiver/child recruitment and enrollment. This will ensure that there is current knowledge of best practices for ADHD diagnosis and care available to all children receiving care for ADHD within this study. The project is not focused on provider training, as these are not new guidelines, but rather addresses other potential barriers that are unique to rural settings. In addition to this clinical training module, all providers will be required to complete training in the provider use of the RAMP platform.

**The RAMP Platform:** The technology platform used for this study will be an adaptation of an existing program used for behavioral health screening for pregnant women. This program has screened close to 400 women and has shown superior clinical outcomes compared to usual care. The RAMP will be housed in REDCap, a HIPAA-compliant data collection tool. The intervention cohort will be notified of their randomization assignment with a text message or email. They will receive text message requests to fill out the RAMP Reports below. Their responses will be compiled into a RAMP Report which will be available to the provider on their dashboard of enrolled participants.

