|-----------|---------------------------|-----------------------|--------------------|------------------|-------------|------------------|-------------|------------------|-------------|------------------|
| 11 Test1  | 1 view    |                       |                    |                  |             |                  |             |                  |             |                  |
| 12 Test2  | None view |                       |                    |                  |             |                  |             |                  |             |                  |
| 13 Test3  | None view |                       |                    |                  |             |                  |             |                  |             |                  |
| 14 Test4  | None view |                       |                    |                  |             |                  |             |                  |             |                  |

**RAMP Platform Prototype. A prototype of the dashboard that providers and research coordinators will use to review participant-entered data and monitor study activities, respectively**

The reports submitted by caregivers will be found on a different tab than those submitted by a teacher (but linked with the same ID) to clearly identify source. Providers and research coordinators will review RAMP Reports from a dashboard similar

to the figure on the right. A red dot will indicate an unreviewed RAMP Report has been entered by the participant. The provider will select the red dot to open the report from the caregiver or teacher. Following review, the provider will answer a quick 2-question, radio-button style survey regarding their response to the report. Research coordinators will be able to monitor data entry, and review and document clinical changes as a result of the report.

**Digital Education Handouts:** Digital education handouts will be sent to all caregivers in the control group on a weekly basis for 4 weeks, then monthly for 2 months. These will be sent through email, and will cover a range of general pediatric topics, such as nutrition, exercise, and screen time.

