### 7.3 LOST TO FOLLOW-UP

The study team will consider caregiver/child dyad participants lost to follow-up if they do not complete the final [study assessment](#). Those who do not complete any [clinical assessments](#) (RAMP Reports or paper assessments)

will still be included if they complete the final [study assessment](#) as this is an intention to treat analysis. To minimize the number of participants lost to follow-up, the study team will contact participants approximately 1 week, 4 weeks, and 2 months after consent to ensure there are no technology issues.

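### A caregiver who confirms opting out of RAMP texts is withdrawn from the whole study, a forced exit that falls on one arm and is tied to rejecting the intervention

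*Protocol*

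**What the plan says.** Section 7.2 describes the trigger: "The text messages sent from the RAMP will give recipients the option to reply" STOP. It continues, "If a caregiver or provider participant opts-out of the text messaging service in this way", a coordinator contacts them to confirm. Then: "Participants that confirm they wish to opt-out of receiving text messages will be withdrawn from the study". Data gathered before exit are kept, and platform access ends. The same section says that a teacher's opt-out leaves the dyad's participation untouched.

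The two arms are reached by different channels. Of the intervention arm, section 6.1.1 says "They will receive text message requests to fill out the RAMP Reports below". Of the control handouts, section 4.2 says "The digital education handouts will be sent via email to the control group and will serve as an attention control", and section 6.1.1 agrees: "These will be sent through email, and will cover a range of general pediatric topics". No equivalent withdrawal rule is given for email.

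On follow-up, section 4.1 has coordinators review charts and "mark how many paper symptom assessments are returned while enrolled on the study for both groups". Section 8.1 counts reports over the 3-month study period. Section 7.3 adds: "The study team will consider caregiver/child dyad participants lost to follow-up if they do not complete the final" study assessment. Section 9.3 defines ITT as everyone randomized, and per-protocol as those in ITT who completed the final study assessment.

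**The concern.** Stopping the texts means no longer using the intervention. It is not the same as leaving the trial, and section 7.2 merges the two. The coordinator is told to confirm one thing, that the caregiver wants no more messages. Nothing indicates that the caregiver has also refused chart review or the Day-90 form. Section 7.1, on discontinuing the intervention, offers no way to stop RAMP and remain in follow-up.

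This matters because section 2.2 makes acceptability of RAMP to caregivers and teachers the first research question, and a confirmed STOP is the plainest negative answer a caregiver can give. The rule ends outcome collection for those families, and only in the arm where the answer can arise. Attrition then depends on arm and on the behavior being measured. That weakens the utilization estimate, which section 9.4.2 calls key for the main trial, and the by-arm comparison of the Day-90 retention marker.

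**Working it through.** **The plan's own figures.** The protocol gives no opt-out rate, so there is no stated figure on this point to reproduce. The nearest is the precision in section 9.2: 12 to 14 points at 90% confidence with n = 36. The Wald half-width is 1.645 × √(p(1−p)/36), which gives 11.9 points at p = 0.25 and 13.7 points at p = 0.50. That statement reproduces and is not disputed.

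**What is lost after a confirmed opt-out, item by item.**
- *Paper forms:* section 4.1 counts them only during enrollment, so abstraction stops at withdrawal. This is an inference from that phrase; section 7.2 does not say it outright.
- *Caregiver RAMP Reports:* a caregiver who wants no texts would send few or none under either rule, so little is lost.
- *Teacher RAMP Reports:* teachers receive their own texts (section 10.1.1) and their reports count toward the primary endpoint. With the dyad withdrawn and its access ended, a willing teacher's later reports would probably be lost too.
- *Day-90 study assessment:* nothing provides for it after withdrawal.

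**Inputs for an illustration.**
- 18 dyads per arm (section 9.2).
- 4 weekly + 2 monthly = 6 requests each to caregiver and teacher, so 12 per dyad (section 6.1.1).
- Return rate 52.7% (section 9.2), so a dyad that stays averages 12 × 0.527 = 6.32 reports.
- Assumed, not in the protocol: an opted-out dyad totals 1 report; k = 2, 3 or 4 opt-outs.

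**Per-protocol set.** Mean over all 18 = ((18 − k) × 6.32 + k × 1)/18. Without the opted-out dyads it is 6.32. The last column is the highest possible Day-90 retention, (18 − k)/18.

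| k | Mean, all 18 | Mean, opt-outs absent | Inflation | Maximum retention |
|---|---|---|---|---|
| 2 | 5.73 | 6.32 | 10% | 89% |
| 3 | 5.44 | 6.32 | 16% | 83% |
| 4 | 5.14 | 6.32 | 23% | 78% |

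Each opt-out is 1/18 = 5.6 points of retention. This is an upper bound on the loss due to the rule, because some of these families would not have returned the form anyway.

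**ITT set.** Here the dyads stay in with truncated counts. If each would have produced q further reports, the arm's mean is understated by k × q/18. For k = 2 and q = 1 that is 0.11 reports per randomized dyad; for k = 4 and q = 2 it is 0.44 (q assumed). If q is above zero, the full count of an opted-out dyad exceeds 1 and the inflation in the table shrinks accordingly.

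**The case against.** A reader might infer that the rule deletes opted-out families from the primary analysis and so inflates the ITT mean by the percentages above. The documents do not support that. Section 9.3 keeps every randomized participant in ITT, and section 7.2 keeps data already collected. In ITT the effect is truncation, which works against RAMP. One loose end remains. Section 7.3 says dyads with no clinical assessments are still included if they complete the final study assessment, and calls this intention to treat. Applied literally, that condition could drop a family that opted out before any report, contrary to section 9.3.

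Other objections stand in part:
- Paper forms in the intervention arm are counted separately and examined in a sensitivity analysis (section 9.4.2), so missing them mainly affects that analysis.
- Per-protocol exclusion applies to any non-completer in either arm. What is particular to this rule is that it makes non-completion certain for opted-out families.
- The confirmation step filters out accidental replies.
- Reasons for withdrawal are documented and discontinuations tabulated, so opt-outs leave a trace, though not as a named acceptability result.
- Control families may withdraw voluntarily, and section 5.5.1 lists an enrollment text without limiting it to one arm. The recurring texts, and hence the practical exposure to the rule, remain on the intervention side.

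**Conclusion.** The point holds as a design weakness that should be corrected. Section 7.2 turns refusal of the intervention's delivery channel into withdrawal from the trial, in one arm, without withdrawal of consent. The two analysis sets are pulled in opposite directions: ITT counts in the intervention arm tend to be understated through truncation, while the per-protocol RAMP mean would be overstated.

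The per-protocol inflation of about 10% to 23% for 2 to 4 opt-outs rests on the protocol's 52.7% return rate and on assumed values for the number of opt-outs and their reports. It does not carry over to ITT. The retention loss is at most 5.6 points per opt-out. The actual number of opt-outs may be small or zero, so these figures show sensitivity and do not predict a bias. That the rule ends follow-up comes from reading the text and does not depend on them.

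**What to change.** In section 7.2, state that a confirmed caregiver text opt-out stops RAMP messaging to that caregiver only. Unless consent is withdrawn:
- the dyad stays in its assigned arm;
- chart abstraction continues, and any teacher reports are counted, to Day 90;
- the Day-90 study assessment is offered by the caregiver's preferred method;
- the dyad is analysed in ITT over the full 3 months.

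Report the number of confirmed opt-outs as an acceptability result. The coordinator's confirmation contact should ask separately whether the caregiver wants to stop texts or to leave the study.

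The cost is a protocol sentence and matching consent wording. Chart review and the Day-90 form are already planned for these dyads.
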